## Abstract

Sarcopenia is a prevalent and debilitating condition among stroke survivors, characterized by the progressive loss of muscle mass and function. This multicenter, randomized controlled trial aims to evaluate the effects of a community-based high-speed power training (HSPT) program tailored for individuals with post-stroke sarcopenia. The intervention bridges the gap between hospital-based rehabilitation and long-term community reintegration by offering physician-supervised, progressive resistance training sessions conducted twice weekly for eight weeks. Participants are assessed on muscle strength, physical performance, balance, body composition, and gait before and after the intervention. The study utilizes validated tools such as handgrip dynamometry, dual-energy X-ray absorptiometry (DXA), short physical performance battery (SPPB), and timed up and go (TUG) to comprehensively evaluate outcomes. Through stratified randomization and a double-blind design, the trial seeks to minimize bias and maximize clinical relevance. The results from this protocol are expected to inform evidence-based guidelines for stroke rehabilitation and support scalable community-based exercise programs aimed at improving functional recovery and quality of life in this population.

## 1. Introduction

Stroke is one of the leading causes of long-term disability and mortality worldwide, significantly impacting the quality of life for survivors. In South Korea alone, approximately 105,000 individuals experience their first or recurrent stroke annually, making stroke a major contributor to the national healthcare burden [1,2]. The recovery period immediately following a stroke is critical, as the central nervous system demonstrates heightened neuroplasticity, enabling substantial functional improvements through targeted interventions [3,4]. However, many stroke survivors face challenges in maintaining effective rehabilitation after hospital discharge, leading to a gap in long-term recovery and community reintegration [5]. In South Korea, many post-stroke patients lose access to rehabilitation programs after hospital discharge due to the limited availability of inpatient rehabilitation beds. This discontinuity may result in functional decline, increased dependency, and reduced community reintegration. According to national reports, community rehabilitation services remain underutilized despite high demand. Therefore, bridging institutional and community-based rehabilitation is critical to ensure continuous support for functional recovery.

Sarcopenia, characterized by a progressive decline in skeletal muscle mass and strength, is prevalent among stroke survivors, with reported rates ranging from 14% to 54% depending on diagnostic criteria and population characteristics [6,7]. Post-stroke sarcopenia presents unique challenges, including rapid muscle atrophy, fiber type alterations, and neuromuscular impairments caused by factors such as disuse, malnutrition, and spasticity [8,9]. These changes affect both paretic and non-paretic limbs, resulting in bilateral functional decline [10]. Addressing sarcopenia is essential for improving mobility, reducing secondary complications, and facilitating successful community reintegration following hospital-based rehabilitation [11,12].

Resistance training is a well-established intervention for mitigating sarcopenia, enhancing muscle strength, mass, and functional performance [13]. Traditional resistance training primarily focuses on slow, controlled movements to strengthen muscle. However, high-speed power training (HSPT) differs significantly in prioritizing the rapid generation of force, which is critical for functional movements such as walking, sit-to-stand transitions, and balance recovery [14]. HSPT specifically targets fast-twitch muscle fibers, which are disproportionately affected in stroke survivors, helping to counteract muscle atrophy and improve reaction time [14,15]. Unlike conventional resistance training, which primarily enhances maximal strength, HSPT improves both strength and explosive power, making it particularly effective in reducing fall risk and enhancing functional independence [14]. Despite its potential, evidence on the application of HSPT specifically for stroke survivors with sarcopenia remains limited.

Community-based interventions are essential for bridging the gap between hospital discharge and long-term rehabilitation. Before participating in such programs, stroke survivors are required to obtain a physician’s referral. Physicians assess the patient’s medical condition, evaluate potential risks associated with exercise, and provide guidance on precautions for community-based exercise programs. This information is incorporated into a referral letter that serves as fitness professionals’ basis for exercise program planning [16,17]. Exercise specialists utilize the physician’s recommendations to design and implement tailored programs that ensure safety and efficacy. This approach minimizes adverse events and optimizes rehabilitation outcomes, particularly for individuals with complex conditions such as post-stroke sarcopenia [15,18]. While endurance-based interventions have been studied, they may not adequately address the rapid type II muscle fiber loss and impaired power output seen in post-stroke sarcopenia. High-speed power training (HSPT) has demonstrated superior outcomes in improving neuromuscular responsiveness, sit-to-stand performance, and fall prevention among older adults and stroke survivors [19,20,21,22,23]. These findings provide a rationale for evaluating HSPT as a specialized approach for mitigating sarcopenia in community settings.

Despite numerous RCTs evaluating resistance training for stroke survivors, most have employed traditional slow-velocity modalities that primarily target maximal strength. These studies often report modest improvements in physical function but lack emphasis on power generation, a key component for mobility and fall prevention [20,21]. Moreover, few trials have adopted community-based frameworks with structured medical oversight. Our protocol addresses these gaps by implementing high-speed power training (HSPT), which has shown superior benefits in older adults and stroke populations in improving explosive strength and dynamic function [22,23]. This study is among the first to evaluate a community-integrated HSPT program tailored for post-stroke sarcopenia, with rigorous outcome assessments and multicenter generalizability.

This study aims to develop and evaluate physician-supervised, community-based high-speed power training for stroke survivors with sarcopenia through a multicenter, randomized controlled trial. By bridging the gap between hospital-based rehabilitation and community life, the protocol offers a structured, accessible, evidence-based intervention that integrates medical oversight. The findings from this study will contribute to the growing body of evidence on sarcopenia management and inform the development of standardized post-stroke rehabilitation strategies, ultimately improving functional outcomes and quality of life for stroke survivors.

## 2. Materials and Methods

### 2.1. Participants

This study will enroll 120 participants, with 30 recruited from each of the four participating institutions. Participants will be recruited from rehabilitation centers, hospitals, and community-based rehabilitation programs. Eligible participants must be adults aged 50 years or older who have been diagnosed with stroke at least six months prior to enrollment. While no upper limit is imposed, the range of post-stroke durations (e.g., 6 months to several years) will be accounted for through stratified randomization via baseline functional status. Participants must be medically stable and cleared by a physician to participate in an exercise program. Additionally, participants must meet the diagnostic criteria for sarcopenia as defined by the European Working Group on Sarcopenia in Older People 2 (EWGSOP2) [24]. According to EWGSOP2, sarcopenia is diagnosed based on the presence of low muscle strength, low muscle mass, and/or poor physical performance, with low muscle strength being the primary determinant.

Muscle strength will be assessed as the primary diagnostic criterion for sarcopenia. Handgrip strength will be measured using a dynamometer, with cut-off values of less than 27 kg for men and 16 kg for women indicating low muscle strength. Alternatively, the five-times sit-to-stand test, which evaluates lower limb strength and functional ability, will be used as an additional criterion, with a time of 15 s or more suggesting muscle weakness.

Muscle mass will be evaluated using bioelectrical impedance analysis (BIA) or dual-energy X-ray absorptiometry (DXA). The appendicular skeletal muscle mass index (SMI) will be calculated by dividing the muscle mass of the upper and lower limbs by height squared (kg/m^2^). According to EWGSOP2 guidelines, a low muscle mass will be defined as an SMI of less than 7.0 kg/m^2^ for men and less than 5.5 kg/m^2^ for women.

Physical performance will be assessed to determine the severity of sarcopenia. Gait speed will be measured using a 4 m walk test, with a walking speed of 0.8 m/s or lower considered indicative of poor physical performance. In addition, the short physical performance battery (SPPB) score will be used as a composite measure of functional performance, including balance, gait speed, and chair stand tests. A total SPPB score of 8 or lower will be considered evidence of poor physical performance and increased sarcopenia severity.

Participants must also be able to walk with or without assistive devices such as a cane or walker.

Exclusion criteria include severe medical conditions that may hinder safe participation, such as uncontrolled cardiovascular disease, unstable angina, or a recent myocardial infarction. Participants with severe musculoskeletal disorders, progressive neurodegenerative diseases (e.g., Parkinson’s disease or amyotrophic lateral sclerosis (ALS)), or uncontrolled diabetes with neuropathy affecting mobility will also be excluded. Cognitive impairment, defined as a Mini-Mental State Examination (MMSE) score < 20, will serve as an exclusion criterion due to its potential impact on adherence and safety. Furthermore, individuals who have engaged in a structured resistance training program within the past three months or have contraindications for exercise, such as severe uncontrolled hypertension (systolic blood pressure ≥ 180 mmHg or diastolic blood pressure ≥ 110 mmHg) or severe osteoporosis with a history of fragility fractures, will not be eligible for participation.

### 2.2. Study Design

This study will be conducted across four medical and rehabilitation centers and follow a randomized, double-blind, parallel-group design to assess the impact of a community-based resistance training program for stroke survivors with sarcopenia. A total of 120 participants will be randomly assigned in a 1:1 ratio to either the intervention group, which will engage in structured resistance training, or the control group, which will continue their routine activities without a structured exercise program. To ensure unbiased results, assessors conducting evaluations will remain blinded to group assignments throughout the study.

The study will be conducted at (1) the National Rehabilitation Center, (2) Bucheon SM Hospital, (3) Korea University Anam Hospital, and (4) the National Health Insurance Service Ilsan Hospital. Participants will be recruited from outpatient rehabilitation programs at these institutions. Eligibility will be confirmed through a pre-screening process, followed by an informed consent procedure to ensure that participants fully understand the study objectives and methodology.

Once enrolled, participants will undergo baseline assessments before randomization. The intervention group will participate in a high-speed power training program designed to enhance muscle strength, functional performance, and mobility. The program will be conducted twice a week for 8 weeks, with each session lasting 60 min and incorporating progressive resistance exercises. Meanwhile, the control group will maintain their regular daily activities without any structured exercise intervention while continuing to receive standard medical care.

Outcome assessments will be conducted at two key time points: before the intervention (baseline) and after completing the 8-week program (post-intervention). The overall study procedure, including recruitment, group allocation, intervention, and assessments, is illustrated in Figure 1. The outcome measures will include muscle strength, physical function, body composition, and cardiopulmonary fitness. The collected data will undergo statistical analysis to evaluate the effectiveness of the resistance training program in mitigating sarcopenia-related functional decline among stroke survivors.

This study follows the SPIRIT guidelines [25] and has been approved by the Institutional Review Board (IRB) of the National Rehabilitation Center (NRC IRB No. 050432021). The study protocol has been registered under Study Registration Number KCT0007521. The findings are expected to provide valuable insights into the role of community-based resistance training in stroke rehabilitation and its potential to enhance post-rehabilitation health outcomes.

### 2.3. Randomization

This study employs a computer-generated, stratified block randomization method to ensure a balanced allocation of participants across study groups. After completing baseline assessments, eligible participants will be randomly assigned in a 1:1 ratio to either the intervention group (high-speed power training program) or the control group (standard care). To maintain allocation concealment, the randomization process will be conducted independently by a statistician who is not involved in participant recruitment, assessment, or intervention delivery.

Randomization will be stratified by study site and baseline functional status to ensure that both groups have comparable distributions of key characteristics. To achieve this, four to six block sizes will be used, and assignments will be sealed in opaque, consecutively numbered envelopes prepared by an independent research assistant. These envelopes will be opened only after the participant is enrolled and their baseline assessment is completed.

To minimize bias, this study follows a double-blind design, where participants and outcome assessors remain unaware of group assignments throughout the study period. Only the exercise specialists administering the intervention will have access to group allocation. Participants will be instructed not to disclose their group assignment to assessors during follow-up evaluations.

This randomization strategy ensures that the study groups remain well balanced, reducing the risk of selection bias and enhancing the reliability of the study findings.

### 2.4. Randomization and Blinding

This study employs a stratified block randomization method to ensure a balanced allocation of participants across the intervention and control groups. Randomization will be stratified by study site and baseline functional status, with block sizes of four to six, to minimize imbalance between groups. An independent statistician who is not involved in participant recruitment, assessment, or intervention delivery will generate the random allocation sequence using computerized randomization software. Group assignments will be sealed in opaque, consecutively numbered envelopes, which will only be opened after participant enrollment and baseline assessment.

To maintain blinding, this study follows a double-blind design, where both participants and outcome assessors will remain unaware of group assignments throughout the study. Only the exercise specialists delivering the intervention will have access to group allocation. Participants will be instructed not to disclose their group assignment during follow-up evaluations to prevent bias.

Additionally, data analysts will be blinded to group assignments during statistical analysis to ensure the unbiased interpretation of results. This randomization and blinding protocol is designed to reduce selection bias, measurement bias, and potential confounding factors, ultimately enhancing the validity and reliability of the study findings.

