However, certain limitations should be acknowledged. The relatively short intervention duration and lack of long-term follow-up are limitations. These factors may affect the generalizability of the findings and limit our ability to assess sustainability. The intervention period is limited to 8 weeks, and longer-term outcomes remain unexplored. Additionally, due to the nature of the intervention, blinding participants is not feasible, which may introduce performance bias. Lastly, heterogeneity in baseline functional status and cognitive ability among stroke survivors may influence intervention adherence and outcomes, despite efforts to standardize implementation. The sustainability of community-based rehabilitation programs depends on the competency and availability of community healthcare workers. In our model, trained exercise specialists deliver the intervention with supervision from physical medicine and rehabilitation (PM&R) physicians. Equipment requirements are minimal and adaptable to local settings. In implementing community-based programs, practical factors such as equipment availability, exercise space, and sustainability must be considered. Future studies should also evaluate the long-term impact of HSPT on sarcopenia and mobility in real-world settings. Stroke survivors with sarcopenia often have reduced exercise tolerance and require greater supervision. Ongoing monitoring by trained community health professionals may improve adherence and maximize intervention outcomes. Future implementation should consider strategies for regular supervision, continued training, and system integration into public health frameworks. Supportive policies, dedicated funding, and infrastructure are also essential to ensure the sustainability and scalable implementation of these programs across communities. Nevertheless, this study is expected to contribute valuable evidence regarding the role of HSPT in stroke rehabilitation, particularly in managing post-stroke sarcopenia. Its findings may inform clinical practice and guide the future development of community-integrated rehabilitation models for improving functional recovery and long-term health in this population.

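### Participants are said to be blinded to their arm, but the comparator is no exercise programme and the article itself says participant blinding is not feasible

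*Protocol article*

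**What the plan says.** The double-blind claim appears in four places in the protocol article, in two forms.

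- **Label only.** The Abstract says: "Through stratified randomization and a double-blind design, the trial seeks to minimize bias and maximize clinical relevance". Section 2.2 says that the trial will "follow a randomized, double-blind, parallel-group design", and then specifies blinding for the assessors alone.
- **Participants named.** Section 2.3 says: "this study follows a double-blind design, where participants and outcome assessors remain unaware of group assignments throughout the study period". Section 2.4 repeats it: "this study follows a double-blind design, where both participants and outcome assessors will remain unaware of group assignments throughout the study". Both sections add that, apart from the exercise specialists, nobody has access to the allocation.

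The control condition in section 2.2 is "the control group, which will continue their routine activities without a structured exercise program". Section 2.8 adds general health education for controls.

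On disclosure, section 2.3 says: "Participants will be instructed not to disclose their group assignment to assessors during follow-up evaluations". Section 2.4 has a near-identical instruction.

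The limitations paragraph of the Discussion says: "due to the nature of the intervention, blinding participants is not feasible, which may introduce performance bias".

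Assessor blinding is stated in sections 2.2, 2.3, 2.4 and 2.7, and analyst blinding in section 2.4.

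**The concern.** The Methods and the Discussion make opposite statements about the same design property, and both cannot be true. The Abstract offers the double-blind design as a reason why bias is kept small, and section 2.4 credits its blinding arrangements with reducing measurement bias. Part of that protection is not there.

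Most of the outcomes are performance tests. A participant who knows that he or she has trained for eight weeks may try harder at the post-intervention visit, and a control who knows that nothing was offered may try less or change activity in the meantime. A blinded assessor does not remove either effect. If the label stays, it can pass into the results paper and into risk-of-bias ratings in later reviews, where a reader of the Abstract alone would not see the limitation.

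**Working it through.** No figure is at issue, so the check sets the statements side by side and asks which of them the design allows.

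**1. Can a participant be unaware of the arm?**
- Intervention arm: two 60-minute sessions a week for 8 weeks (sections 2.2, 2.5 and 2.6). 2 × 8 = 16 sessions, which agrees with the number given in section 2.7.
- Control arm: usual activities without a structured exercise programme (sections 2.2 and 2.5), with general health education (section 2.8). No sham or attention-matched exercise is described.
- Consent: participants are to understand the study's aims and methods (section 2.2) and are told its procedures (section 2.5).

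Someone who understands the study and either attends or does not attend 16 training sessions knows the arm. The answer is no.

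**2. Are the blinding sections consistent within themselves?**
- Sections 2.3 and 2.4 say that participants do not know their assignment, and also instruct them not to reveal it. The instruction makes sense only if they know it.
- Both sections limit access to the allocation to the exercise specialists. The participants whom those specialists train necessarily know it as well.

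**3. Which statement survives?** The design in step 1 and the instruction in step 2 both agree with the Discussion and disagree with sections 2.3 and 2.4. The false statement is the one in the Methods.

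**4. Which kinds of blinding are affected?**

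| Group | Stated as blinded | Contradicted |
|---|---|---|
| Participants | 2.3, 2.4 (label in Abstract, 2.2) | Yes: Discussion, comparator, non-disclosure instruction |
| Outcome assessors | 2.2, 2.3, 2.4, 2.7 | No |
| Data analysts | 2.4 | No |
| Exercise specialists | Stated as unblinded in 2.3, 2.4 | Not applicable |

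**5. How many outcomes are exposed?** Table 3 lists eight tools. Six need voluntary effort: handgrip, isokinetic strength, SPPB, BBS, TUG and 10MWT. Two do not: DXA and BIA. That is 6 of 8.

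**The case against.** The strongest defence is that the article already discloses the problem: the Discussion says that participants cannot be blinded and names the consequence. The Abstract and section 2.2 use only a label, and section 2.2 goes on to specify assessor blinding alone, so the label might be read there as assessors plus analysts. An unblinded participant is also unavoidable with this comparator, and correcting the text changes neither allocation, sample size, outcomes nor analysis.

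Much of this stands. A reader of the whole article is told of the risk, the outright false statement is confined to sections 2.3 and 2.4, and the comparator itself is not at fault. It does not rescue those two sections, which name participants explicitly, or the Abstract, which presents the label as protection against bias with no qualification. Nor does condensation into a journal article explain it: the text asserts both positions and does not merely omit one.

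A reader might go further and infer that assessor blinding has failed too. The article does not support that. Assessor blinding now relies on participants keeping silent, but it is stated consistently and nothing contradicts it. A reader might also want to put a size on the expectation effect, or to use DXA as a check on it. The article gives no figure from which a size could be derived. DXA measures lean mass and fat, whereas the programme aims at rapid force production, so function could improve without a change on DXA.

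**Conclusion.** The point holds as a false statement of a design property: participants are not blinded, by the article's own admission and by the nature of the two arms. It is an error of description and does not show that the results will be biased. Its reach is six of the eight tools in Table 3, for which the trial can claim protection from blinded assessors and analysts but not from participants' knowledge of their arm. The size of any expectation effect is unknown, and none is assumed here. The conclusion rests on one assumption beyond the text: that a participant in a study without sham exercise can tell whether he or she has been given a training programme. The correction should be made before results are reported, because it determines what bias protection the trial may claim.

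**What to change.** 1. In the Abstract and sections 2.2, 2.3 and 2.4, replace the double-blind label with: *assessor- and analyst-blinded; participants and exercise specialists unblinded*.
2. In sections 2.3 and 2.4, delete the statements that participants are unaware of their assignment.
3. In the same two sections, correct the sentences that restrict knowledge of the allocation to the exercise specialists, so that they include participants.
4. Keep the instruction to participants not to reveal their arm to assessors. It is what assessor blinding depends on.
5. Carry the performance-bias limitation from the Discussion into the conclusions drawn on handgrip, isokinetic strength, SPPB, BBS, TUG and 10MWT.

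Optionally, assessors could record their guess of the allocation at the post-intervention visit. Assessor blinding is not in dispute, so this is not needed to resolve the contradiction.

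The cost is a wording amendment, plus one item on the post-visit form if the optional step is taken. Treatment, schedule, sample size and analysis do not change. The price is a more modest claim about protection from bias.
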